#### Blood pressure

Following ≥5 min of seated rest, three consecutive blood pressure measurements will be performed using an automatic cuff (Omron, Kyoto, Japan), with a 1 min interval between measurements. The last two measures will be averaged to obtain mean HR, mean systolic blood pressure and mean diastolic blood pressure.

#### Protocol adherence

For participants in the intervention group, adherence to the RT protocol will be monitored via the Technogym application (Technogym, Cesena, Italy), which allows participants to log both completion of the home-based and supervised RT sessions. Additionally, adherence to the home-based RT protocol will be assessed using an online single question survey (Castor EDC, Castor). Attendance at the supervised RT sessions will be recorded using an attendance list. Adherence to the whey protein supplementation will be assessed using a brief weekly online survey (Castor EDC, Castor).

### Questionnaires

After each measurement visit (ie, baseline, 3, 6 and 12 months postoperatively), participants will receive an email with a personal weblink to an online questionnaire (Castor EDC, Castor) to assess HRQoL and gastrointestinal symptoms and a separate weblink to an online Food Frequency Questionnaire (FFQ tool, Wageningen University and Research, Wageningen, The Netherlands). In addition to the online questionnaires, a brief set of structured questions will be asked in person during each measurement visit. These questions address current engagement in RT (eg, type of exercise and frequency), weekly performance of light, moderate and vigorous PA and prior use of glucagon-like peptide 1 receptor agonists for weight loss.

#### Health-related quality of life

HRQoL will be evaluated using the OBESI-Q, a translated subset of the BODY-Q questionnaire, a validated patient-reported outcome instrument that is especially designed to measure a patient’s perception on weight loss and/or body contouring.^31^ The OBESI-Q questionnaire is designed to evaluate HRQoL in patients with obesity through 54-point Likert-scale (*Completely disagree* to *Completely agree* or *Never* to *Always*) questions, divided over five subscales: *eating behaviour, social function, psychological function, physical function* and *body image*. For each subscale, a sum score will be calculated. As part of the standard perioperative care at the NOK, patients are asked to fill in the OBESI-Q at baseline and after 12 months of follow-up. These data will be extracted from the electronic health record. A shortened version of the OBESI-Q will be sent from Castor EDC at 3 and 6 months postoperatively, including the subscales eating behaviour, physical function and body image, as we anticipate observing the most pronounced changes within these domains in response to our intervention.

In addition to the OBESI-Q, the five-level EuroQol five-dimensions (EQ-5D-5L) questionnaire will be administered orally during each measurement visit to assess HRQoL. The EQ-5D-5L is a validated instrument suitable for use in cost-effectiveness analyses.^32 33^

#### Gastrointestinal tolerability

Gastrointestinal tolerability of the protein supplementation will be assessed using the Gastrointestinal Symptoms Rating Scale (GSRS).^34^ The GRSR is a validated questionnaire, consisting of 15 questions on a 7-point Likert scale (*no discomfort at all* to *very severe discomfort*), divided over five subscales: *reflux, abdominal pain, indigestion, diarrhoea* and *constipation*. For each subscale, a sum score will be calculated.

#### Habitual dietary intake

Habitual dietary intake will be assessed using an online FFQ (FQ13, Wageningen University & Research), a validated questionnaire to assess nutrient intake.^35 36^ This information will be used to calculate total energy intake and intake of macronutrients and micronutrients.

### Data management

All data will be stored in a digital research environment (myDRE, anDREa, Nijmegen, The Netherlands) for at least 15 years, adhering to the General Data Protection Regulation, Good Clinical Practice and Good Laboratory Practice guidelines. Standard software packages will be used for data handling and statistical analyses (eg, Castor EDC, IBM SPSS, R, Microsoft Excel). A comprehensive data catalogue is presented in table 2. In line with open science and the findable, accessible, interoperable and reusable (FAIR) principles, inquiries for reuse of the ENRICHED data can be directed to the corresponding author.

**Table 2 T2:** Data catalogue table of the ENRICHED study

Category	Subcategory	Variables
Baseline characteristics	Study inclusion	Allergic or sensitive to dairy proteins, or lactose intolerant (yes/no); diagnosed renal insufficiency (yes/no); diagnosed intestinal disease influencing uptake of protein (yes/no); inability to perform any resistance exercises (yes/no); previous MBS (yes/no); presence of medical devices which are contraindicated for BIA (yes/no); age >18 (yes/no); MBS scheduled (yes/no); able to understand and perform study procedures (yes/no); inclusion criteria met (yes/no); informed consent signed (yes/no); date of informed consent (dd-mm-yyyy).
	Demographics	Year of birth (yyyy); sex (female/male); medical history (text); Charlson Comorbidity Index (none/myocardial infarction/congestive heart failure/peripheral vascular disease/cerebrovascular disease (CVA or TIA)/dementia/chronic pulmonary disease/peptic ulcer disease/mild liver disease/hemiplegia/moderate-to-severe chronic kidney disease/tumour without metastasis/tumour with metastasis/leukaemia/lymphoma/HIV or AIDS/connective tissue disease/diabetes without organ damage/diabetes with organ damage/other (text).
	Randomisation	Intervention or control group (intervention group/control group); subgroup (yes/no).
Surgery	Surgery characteristics	Date of surgery (dd-mm-yyyy); type of surgery (RYGB/SG).
Measurements	Visit information	Date of visit (dd-mm-yyyy).
	Exercise characteristics	Do you usually do muscle-strengthening exercises (yes/no); if yes: how many days, in a usual week, do you do muscle-strengthening exercise (0/1/2/3/4/5/6/7); and: which type of muscle-strengthening exercise do you do (holistic exercises/body weight exercises/resistance band or free weights/weight machines)?
	Regular physical activity	Do you carry out light/moderate/vigorous physical activity on a regular basis (yes/no); if yes: how many days a week do you carry out light/moderate/vigorous physical activity (days/week); and: on those days, how many min a day do you do light/moderate/vigorous physical activity (min/day)?
	Previous GLP-1 use	Have you previously used GLP-1 medication (yes/no); if yes: which type of GLP-1 medication have you used (liraglutide (Saxenda)/semaglutide (Ozempic/Wegovy)/tirzepatide (Mounjaro)/I do not know); and: for how long did you use this medication (months); and: how much weight did you lose while using this medication (kg)?
	Healthcare consumption	In the past 3 months, have you had one or more appointments with any of the following healthcare providers (general practitioner/medical specialist/paramedical healthcare provider (please specify)/none of the above); if yes: how many appointments have you had in the past 3 months; in the past 3 months, have you visited a hospital or another type of healthcare facility (no/yes, a hospital/yes, another type of healthcare facility (please specify); if yes: what was the purpose of your visit (day treatment/inpatient admission/outpatient consultation); if ‘inpatient admission’: how many days were you admitted to the hospital or healthcare facility (days); did you undergo a medical procedure during your visit (yes/no)?
	Patient-reported health	Mobility (I have no/slight/moderate/severe problems walking or I am unable to walk); ability to wash or dress yourself (I have no/slight/moderate/severe problems washing or dressing myself or I am unable to wash or dress myself); ability to perform your daily activities (I have no/slight/moderate/severe problems performing my daily activities or I am unable to perform my daily activities); level of pain or discomfort (I have no/slight/moderate/severe/extreme pain or discomfort); emotional state (I am not/slightly/moderately/severely/extremely anxious or depressed).
	Multivitamins	Use of (multi)vitamins (no multivitamins/Fit For Me (RYGB)/Elan (RYGB)/vitamins on prescription (RYGB)/Flinndal (RYGB)/Lucovitaal WLS (RYGB)/Fit For Me (SG)/Elan (SG)/vitamins on prescription (SG)/Flinndal (SG)/house brand vitamins/other (text); if not ‘No multivitamins’; dosage (multi)vitamins (two tablets per day/one tablet per day/five to six tablets per week/three to four tablets per week/one to two tablets per week). Calcium and vitamin D supplement use (no calcium and vitD/500 mg calcium and 400IE vitD/500 mg calcium and 800IE vitD/1000 mg calcium and 800IE vitD/Other (text); if not ‘No calcium and vitD’; dosage calcium and vitD supplements (four tablets per day/three tablets per day/two tablets per day/one tablet per day/five to six tablets per week/three to four tablets per week/one to two tablets per week).
	Body composition	Height (cm); weight (kg); BMI (kg/m^2^); waist circumference (cm); fat mass (kg); fat mass (%); fat-free mass (kg); fat-free mass (%); fat-free mass right arm (kg); fat-free mass left arm (kg); fat-free mass trunk (kg); fat-free mass right leg (kg); fat-free mass left leg (kg).
	Physical tests	Handgrip measurements: handgrip right hand first measurement (kg); handgrip right hand second measurement (kg); handgrip left hand first measurement (kg); handgrip left hand second measurement (kg). Leg extension measurement: bilateral maximum isometric strength (kg); bilateral maximum power (Watt); bilateral maximum power acceleration (deg/s). SPPB: balance feet together during 10 s (yes/no); if yes: balance semitandem during 10 s (yes/no); if yes: balance full tandem (seconds); time 4 m walk (seconds); time chair stand (seconds); SPPB score (scale 0–12). Åstrand ergometer test: use of beta blockers (yes/no); if no: wattage at finish (Watt); mean heart rate 5th and 6th min (bpm); Borg RPE scale at finish (scale 6–20); predicted VO^2^ max (absolute VO^2^ max) (L/min); predicted VO^2^ max per kg (relative VO^2^ max) (L/min/kg).
	Blood pressure	Heart rate at rest (bpm); systolic blood pressure at rest (mm Hg); diastolic blood pressure at rest (mm Hg).
	Blood sample	Blood sample drawn (yes/no); if yes: date of blood sample drawn (dd-mm-yyyy); if no: reason no blood drawn (text).

BIA, bioelectrical impedance analysis; BMI, body mass index; bpm, beats per minute; cm, centimetres; CVA, cerebrovascular accident; ENRICHED, EffectiveNess of pRotein supplementatIon Combined witH resistance Exercise training to counteract Disproportional fat-free mass loss following metabolic–bariatric surgery; GLP-1, glucagon-like peptide 1; kg, kilograms; L, litres; MBS, metabolic–bariatric surgery; min, minutes; RPE, rating of perceived exertion; RYGB, Roux-en-Y gastric bypass; SG, sleeve gastrectomy; SPPB, Short Physical Performance Battery; TIA, transient ischaemic attack; vit, vitamin; VO_2_ Max, maximum uptake of oxygen; WLS, weight loss surgery.

### Sample size

Sample size calculation is based on the primary outcome of FFML/TWL ≥30% at 3 months post-MBS. The power analysis was based on differences between two independent groups (intervention group vs control group). We consider our intervention successful if we find an expected difference in prevalence of disproportional FFML of 26%^5^ versus 14% between the control and intervention group, respectively. Based on a two-sided test with α=0.05 and a power of 80%, 174 participants per study arm are needed to show this difference. Accounting for a 10% drop-out rate, a total of 400 participants will be recruited (200 per study arm). Calculations were performed using G-power V.3.1.2. (University of Düsseldorf, Düsseldorf, Germany)

### Statistical analysis

Statistical analyses will be performed using R. Collected data will be checked for completeness and normality. Continuous parametric data will be displayed as mean±SD, non-parametric data as median (IQR) and categorical data as frequency with percentage. All statistical tests will be two-sided, and significance is set at p<0.05.

Descriptive analyses will be performed to explore the variance in the study parameters and calculate the baseline characteristics of the study population. For the primary analysis, an intention-to-treat approach will be used. Generalised estimating equations will be used for dichotomous outcomes grouped by patient ID to account for repeated measurements, including an adjustment for NOK centre and, if possible, adjusted for the baseline value of the outcome variable. A similar approach will be used for continuous outcomes using linear mixed-models analyses with a random intercept for patient ID to account for repeated measurements. The intervention effects will be evaluated for all follow-up time points by including a dummy variable for each time point and repeating the analyses with a different reference time point. Potential effect modification will be evaluated for sex, age group (age <50 years and age ≥50 years), type of surgery, study site and postmenopausal status (in female participants). A variable is treated as an effect modifier when its interaction term with the independent variable has a p value <0.10. When effect modification is observed, stratified results will be reported in addition to the overall results. Additionally, confounding will be evaluated for sex, age, baseline BMI, treatment adherence and type of surgery by including each variable in the model separately. Sensitivity analyses will be conducted to assess the robustness of the findings.

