### Randomisation, blinding and treatment allocation

A total of 400 patients will be enrolled and randomly assigned in a 1:1 ratio to either the intervention or control group. Randomisation will be stratified by sex to ensure a balanced sample across both groups, which does not imply equal representation of men and women. A computerised randomisation system (Castor Electronic Data Capture (EDC), Castor, Amsterdam, the Netherlands) will be used with variable block sizes of 16 and 24 to ensure allocation concealment. A subgroup of 100 patients will undergo additional measurements, including dual-energy X-ray absorptiometry (DXA) for body composition assessment and objective PA measurements using thigh-worn accelerometry. Blinding of the patients, involved healthcare professionals and outcome assessors is not possible due to the nature of the intervention.

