### Outcome measures

The primary outcome is the difference in proportion of patients with disproportional FFML/TWL (ie, ≥30%) in the intervention group compared with the control group at 3 months post-MBS. Secondary outcomes are postintervention differences in body composition, muscle strength and function, cardiorespiratory fitness, (cardio)metabolic health, HRQoL, gastrointestinal discomfort, cost-effectiveness of the intervention and treatment satisfaction in the intervention group. Most outcomes are measured preoperatively and at 3, 6 and 12 months post-MBS. Cost data are assessed preoperatively and at 6 and 12 months post MBS, and treatment satisfaction is assessed after the 6-month intervention period. Cost and outcome data are used to calculate the incremental cost-effectiveness of the intervention in terms of cost per successfully treated patient using a time horizon of 1 year.

The primary outcome was set at 3 months post-MBS as previous studies have shown that the most pronounced changes in body composition, including substantial reduction in FFM, occur during this early postoperative phase.^5 23^ Our intervention, combining RT and protein supplementation, was specifically designed to target this critical period. Secondary outcomes will be assessed at 6 and 12 months to assess the persistence of potential effects over time.

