### Measurements

#### Anthropometrics and body composition

Body height and weight will be measured during each measurement visit, using a stadiometer (BSM 170B, InBody, Seoul, South Korea) and will be reported to the nearest 1 mm. Body weight (kg) will be measured using a bioelectrical impedance machine (InBody 770, Seoul, South Korea).^24^ Both measurements will be used to calculate BMI (kg/m^2^). Waist circumference (cm) will be measured midway between the lower rib margin and iliac crest.

Body composition will be assessed in the entire study population by bioelectrical impedance analysis (BIA) (InBody 770, Seoul, South Korea), which can distinguish between FM and FFM. BIA is a validated, low-cost and readily available technique for assessing body composition changes in longitudinal study designs.^25^ Weight loss, FM loss and FFML between preoperative and follow-up assessments will be determined, and the FFML/TWL will be calculated as the absolute FFML (kg) divided by TWL (kg) × 100%.

DXA measurements (Hologic Horizon A, Marlborough, Massachusetts, USA) will be performed in the subgroup (n=100) before and 3 months after surgery, as this is considered the gold standard for measuring body composition. Within the same subgroup, an additional BIA measurement using a different device (TANITA DC-360, Amsterdam, the Netherlands) will be conducted to validate the different methods of body composition assessment.

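### The primary GEE leaves out sex, the only stated stratifier, and for FFML/TWL centre is its only working baseline covariate; the test is slightly conservative, not biased

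*Protocol article*

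**What the plan says.** All references are to the Protocol article.

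- **Stratifier.** Randomisation, blinding and treatment allocation: "Randomisation will be stratified by sex to ensure a balanced sample across both groups". No other stratification factor is named. The same section states: "A total of 400 patients will be enrolled and randomly assigned in a 1:1 ratio".
- **Primary outcome.** The section on outcome measures gives this definition: "The primary outcome is the difference in proportion of patients with disproportional FFML/TWL (ie, ≥30%) in the intervention group compared with the control group". The time point is 3 months after surgery.
- **How FFML/TWL is formed.** Anthropometrics and body composition: "Weight loss, FM loss and FFML between preoperative and follow-up assessments will be determined". The ratio is then absolute fat-free mass loss divided by total weight loss.
- **Model covariates.** Statistical analysis, for dichotomous outcomes: "including an adjustment for NOK centre and, if possible, adjusted for the baseline value of the outcome variable". Continuous outcomes are handled in a similar way with mixed models.
- **Where sex appears in the analysis.** In the same section, as a candidate effect modifier ("Potential effect modification will be evaluated for sex, age group") and in a further check: "Additionally, confounding will be evaluated for sex, age, baseline BMI, treatment adherence and type of surgery by including each variable in the model separately".

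**The concern.** The design balances the arms on sex, but the stated covariate set for the primary model does not contain sex. It contains centre, which is not a stated stratifier, and a baseline value of the outcome that FFML/TWL cannot have, because no loss has occurred at the preoperative visit. What remains is a primary model with centre as its only baseline covariate.

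If sex predicts disproportional fat-free mass loss, stratification removes the between-sex component from the true sampling variance of the arm difference. A model without sex still counts that component in its standard error. The standard error is then too large, the test rejects less often than its nominal 5% under the null, and some power is lost in a trial sized at 80%. Checking sex later as a confounder does not repair this, because sex is balanced by design and the check does not put it into the primary model.

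This is more than a detail left to an analysis plan: the article states a covariate set and gives the stratifier a different role.

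**Working it through.** **1. The plan's own figure.** Inputs from Sample size: 26% in control "versus 14% between the control and intervention group, respectively", two-sided α = 0.05, power 80%. Pooled-variance formula without continuity correction:

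n = [1.960·√(2·0.20·0.80) + 0.842·√(0.26·0.74 + 0.14·0.86)]² / 0.12² = (1.109 + 0.471)² / 0.0144 ≈ 173.2, so 174 per arm.

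This matches the article. With 10% loss, 348/0.90 = 387, rounded up there to 400. From 200 per arm, 200 × 0.90 = 180 remain evaluable, and the same formula gives 81.5% power. The calculation uses no covariates, so nothing below changes it.

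**2. Assumptions.** The documents do not give the share of men or the association of sex with FFML/TWL ≥30%. Assumed: 20% or 30% men, and a sex odds ratio (men v women) of 1 to 5. Marginal rates are held at 26% and 14%, with 180 per arm balanced within sex. As a simplification, the check is a logistic Wald test at 3 months, without centre or the later visits.

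**3. Type I error without sex.** Let w be the share of each sex and p its event rate under the null (both arms at 26%). The ratio of true variance to the variance that the model reports is

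r = Σ w·p(1−p) / (0.26·0.74), and actual type I error = 2·Φ(−1.960/√r).

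Example with 20% men and odds ratio 3: rates are 21.3% in women and 44.8% in men (0.8·0.213 + 0.2·0.448 = 0.26). Then r = (0.8·0.213·0.787 + 0.2·0.448·0.552)/0.1924 = 0.1836/0.1924 = 0.954, and type I error = 2·Φ(−2.007) = 4.5%.

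**4. Power without and with sex.**

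- Without sex: Φ((L − 1.960·SE_model)/SE_true). L = logit(0.26) − logit(0.14) = 0.769. SE_model = √[1/(180·0.1924) + 1/(180·0.1204)] = 0.274. SE_true uses the within-sex variances. With odds ratio 1 the two SEs agree, and power = Φ(0.769/0.274 − 1.960) = 80.2%. This is lower than 81.5% only because it is a Wald test on the log-odds scale.
- With sex: Φ(|θ|/√V − 1.960). θ is the within-sex log odds ratio for arm, and V is its variance from the information matrix of the model with arm and sex.

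| Sex odds ratio | Type I error without sex (20% / 30% men) | Power without sex | Power with sex |
|---|---|---|---|
| 1 | 5.0% / 5.0% | 80.2% / 80.2% | 80.2% / 80.2% |
| 1.5 | 4.9% / 4.9% | 80.3% / 80.3% | 80.4% / 80.4% |
| 2 | 4.8% / 4.8% | 80.4% / 80.4% | 80.8% / 80.9% |
| 3 | 4.5% / 4.4% | 80.7% / 80.7% | 81.7% / 81.9% |
| 5 | 3.9% / 3.7% | 81.3% / 81.4% | 83.5% / 83.9% |

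From the unrounded values, the gain from adding sex is 0 to 1.2 points for odds ratios 1 to 3, and 2.2 to 2.5 points at odds ratio 5.

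**The case against.** The strongest reply is that little is at stake. Leaving out a balanced stratifier is safe in direction, 174 per arm reproduces exactly, adjusting for centre in a two-centre trial is ordinary, and further covariates are an efficiency choice. All of that stands and limits the size of the point. It does not remove the mismatch between the stratified design and the stated covariate set.

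A reader might infer several stronger things that the documents do not support:

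- **That the plan adjusts the primary outcome for a value that does not exist.** The baseline adjustment is conditional on being possible, and the sentence covers all dichotomous outcomes. For FFML/TWL the condition is simply not met. What remains is that no substitute is named.
- **That a large power gain is being lost.** A simulation with 180 per arm, 20% men, and sex plus one preoperative covariate jointly explaining 10, 20 or 30% of the latent variance moves power from 82% to 84%, 82% to 86% and 81% to 88%. Those shares of variance are assumed, and the gain cannot be credited to sex alone.
- **That the confounder checks create rival primary estimates.** The section sets out one base model and adds the checks to it. Nothing says that a checked model replaces the primary result.
- **That the checks mislead because odds ratios are non-collapsible.** This would need a logit link. The article names no link, and a difference in proportions can be estimated with an identity link.
- **That scheduled surgery type is ready to use as a covariate.** Table 2 lists type of surgery next to the date of surgery. Its only scheduling item is whether surgery is scheduled.

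**Conclusion.** The point holds as a modest specification fault. The only stated stratifier is outside the primary model, and for FFML/TWL the stated covariates reduce to centre. There is no bias, no inflation of type I error and no effect on the stated sample size.

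The cost is a slightly conservative test: actual type I error between 5.0% and 3.7%, and 0 to 2.5 power points forgone, with more than 1.2 points only when sex is very strongly prognostic. These figures rest on the assumed 20–30% men and on odds ratios of 1 to 5 with men at the higher risk; the documents fix neither. A preoperative body-composition or weight covariate could add further precision, by an amount that depends on prognostic strength the documents do not give.

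**What to change.** In Statistical analysis:

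1. Name sex alongside centre as a prespecified covariate in the primary GEE.
2. State that FFML/TWL has no baseline value, and name the preoperative measure used in its place, for example fat-free mass, or weight or BMI.
3. State that the 3-month contrast from this single model is the primary estimate, reported as a difference in proportions to match Outcome measures. If a logit link is chosen, obtain the difference by standardising the model's predicted proportions over the trial population.
4. Label the one-at-a-time covariate checks as supportive only.

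The cost is wording. Table 2 already lists sex, weight, BMI and fat-free mass, and no change to the sample size or visits is needed. The choice should be fixed before outcome data by arm are examined.

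### For continuous secondary outcomes the plan names only a random intercept per patient. Unless visit-specific variances or robust standard errors are added, effects at 3, 6 and 12 months share one variance.

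*Protocol article*

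**What the plan says.** The Statistical analysis section of the protocol article prescribes, for continuous outcomes, "linear mixed-models analyses with a random intercept for patient ID to account for repeated measurements". Visit-specific results come from the same model: "The intervention effects will be evaluated for all follow-up time points by including a dummy variable for each time point", with the fit repeated under another reference visit. Baseline adjustment is written for the dichotomous outcomes ("if possible, adjusted for the baseline value of the outcome variable") and carries over because the continuous outcomes are to be handled in a similar way.

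On timing, Outcome measures states: "Most outcomes are measured preoperatively and at 3, 6 and 12 months post-MBS". On the body-composition variables, Anthropometrics and body composition states: "Weight loss, FM loss and FFML between preoperative and follow-up assessments will be determined". Each follow-up value is therefore a cumulative change from before surgery.

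No random slope, visit-specific residual variance, unstructured covariance or robust standard error is named. The nearest safeguard is general: "Sensitivity analyses will be conducted to assess the robustness of the findings". The article reports no SD at any visit.

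**The concern.** A random intercept with independent, equal-variance residuals is a compound-symmetry model: every visit has the same variance and every pair of visits the same correlation. The visit indicators free the means, not the variances. Changing the reference visit only re-expresses the same fit. Baseline adjustment removes differences in starting level but does not let the remaining spread differ by visit.

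The trial gives some reason to expect unequal spread. Losses accumulate over unequal spans. Two operations are pooled. Supervised training and extra dietetic counselling stop after the 6-month intervention. Controls are free to train or take protein, and the Discussion expects adherence to vary. If spread does grow, the pooled variance is too large at 3 months, the period the article calls critical. It is too small at 12 months, where persistence of effect is judged. The first costs precision for the continuous body-composition outcomes; the second produces too many false-positive persistence findings at the stated 5% level.

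**Working it through.** **The plan's own figure.** The only stated calculation concerns the binary primary outcome: "prevalence of disproportional FFML of 26%^5^ versus 14% between the control and intervention group" and "Based on a two-sided test with α=0.05 and a power of 80%, 174 participants per study arm are needed to show this difference". With pooled proportion 0.20:

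n = [1.960·√(2·0.20·0.80) + 0.8416·√(0.26·0.74 + 0.14·0.86)]² / 0.12² = (1.1087 + 0.4707)² / 0.0144 ≈ 173.2, rounded up to 174 per arm.

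174/0.9 = 193.3, so 194 per arm or 388 in total, which the planned 400 covers. The figure reproduces and does not bear on the continuous-outcome model, for which the article gives no figure.

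**Inputs for this point.**
- From the article: the random-intercept model, three follow-up visits, 200 per arm, 10% drop-out, two-sided 5% level.
- Assumed, because the article gives none: the ratio of baseline-adjusted SDs at 3:6:12 months.
- Assumed: default residuals (independent, equal variance).

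**Formula.** With complete data, the variance fitted at every visit is the mean of the three visit variances. Hence

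r(t) = model SE / true SE at visit t = √(mean of the three variances / variance at t),

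type I error at t = 2·[1 − Φ(1.96·r(t))], and 95% CI coverage is 1 minus this.

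**Worked case, SD ratio 1 : 1.25 : 1.5.** Variances 1, 1.5625 and 2.25; mean 4.8125/3 = 1.604; square root 1.267. So r = 1.267 at 3 months, 1.267/1.25 = 1.013 at 6 and 1.267/1.5 = 0.844 at 12.

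| SD ratio 3:6:12 months | r at 3 / 6 / 12 | Coverage at 3 / 6 / 12 (%) | Type I error at 3 / 12 (%) |
|---|---|---|---|
| 1 : 1 : 1 | 1.00 / 1.00 / 1.00 | 95.0 / 95.0 / 95.0 | 5.0 / 5.0 |
| 1 : 1.1 : 1.2 | 1.10 / 1.00 / 0.92 | 96.9 / 95.1 / 92.8 | 3.1 / 7.2 |
| 1 : 1.25 : 1.5 | 1.27 / 1.01 / 0.84 | 98.7 / 95.3 / 90.2 | 1.3 / 9.8 |
| 1 : 1.4 : 1.75 | 1.42 / 1.01 / 0.81 | 99.5 / 95.3 / 88.8 | 0.5 / 11.3 |
| 1 : 1.5 : 2 | 1.56 / 1.04 / 0.78 | 99.8 / 95.8 / 87.2 | 0.2 / 12.8 |

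The formula is symmetric: with SDs falling as 1.2 : 1.1 : 1, r is 0.92 at 3 months and 1.10 at 12.

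**What the 3-month excess costs.** Take an effect with 80% power under a correct SE, so an expected z of 1.960 + 0.842 = 2.802. Its power under the model is Φ(2.802 − 1.960·r). For r = 1.103 this is Φ(0.640) ≈ 74%; for r = 1.555 it is Φ(−0.246) ≈ 40%.

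**Simulation check.** Random-intercept REML fits with 200 per arm, drop-out reaching 10% by 12 months, a baseline covariate and separate arm effects by visit; 2,000 simulated trials per case, adjacent-visit correlation 0.6 and 0.85. Coverage at 3 / 6 / 12 months:
- 1 : 1 : 1: 95.3 / 95.0 / 95.3% and 95.0 / 94.6 / 95.0%
- 1 : 1.1 : 1.2: 97.2 / 95.4 / 93.4% and 96.6 / 95.6 / 92.4%
- 1 : 1.25 : 1.5: 98.6 / 95.6 / 89.8% and 98.5 / 95.0 / 90.1%
- 1 : 1.5 : 2: 99.8 / 94.6 / 85.0% and 99.8 / 95.2 / 86.6%

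This agrees with the formula. At the top of the range the simulated 12-month coverage is slightly lower than the formula gives. The formula assumes complete data, whereas the simulation loses more 12-month than 3-month values, which is the likely reason.

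**The case against.** The strongest objection is that the article names a random intercept but does not exclude anything else. Such a model can carry visit-specific residual variances or robust standard errors without contradicting the text, and an analysis plan that is not shown may specify them. That stands. A reader might infer that the plan forces one variance on all visits; the text supports only that it does so if the default is used.

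A reader might also contrast a GEE protected by robust errors with an unprotected mixed model. The article mentions robust errors for neither, so the contrast has no basis in the text.

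The growth in spread is assumed. The Outcome measures section says the largest body-composition changes come early. That describes means rather than spread, but it gives no support for a steep rise in SD. A larger headline figure is easy to produce: SDs of 4, 6 and 9 kg give r of 1.66 and 0.74 and a 12-month type I error of about 14.7%. That is a 12-month to 3-month ratio of 2.25, outside the range used here and without support in the documents.

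Finally, the argument for growing spread applies to cumulative weight, fat-mass and fat-free-mass change. No similar reason is given for strength, fitness, blood pressure, blood markers or questionnaire scores. What survives is that the article does choose a specific model, and that this model at its default is valid for visit-specific effects only if the visit variances are equal.

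**Conclusion.** The point holds as a modest, conditional weakness in the analysis of continuous secondary outcomes. It rests on two assumptions: default residuals, and unequal spread across visits. For a 12-month to 3-month SD ratio of 1.2 to 2, confidence intervals are about 10% to 56% too wide at 3 months and about 8% to 22% too narrow at 12 months; 6 months is nearly correct. The practical risk is an over-confident persistence claim at 12 months and lost precision at 3 months. At equal SDs there is no error.

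A reader might take the loss of power at 3 months as a threat to the primary test. It is not one: the primary outcome is binary and analysed by GEE, and the sample size was computed for that outcome. DXA has a single follow-up visit, so nothing is pooled over visits there.

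**What to change.** For continuous outcomes measured at all three follow-up visits, replace the random-intercept model with a repeated-measures mixed model using an unstructured within-patient covariance, with arm-by-visit and baseline-by-visit terms. State a fallback in advance: heterogeneous compound symmetry, or robust standard errors, if the model does not converge.

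This allows the SDs to rise, fall or stay equal, so the sponsor need not settle the assumption first. It needs six covariance parameters (three variances and three correlations) with 400 patients planned. The cost is a sentence or two in the analysis plan and a changed model specification in the R code. The downside is a small convergence risk, mainly for sparse outcomes, which the fallback covers. Recruitment is expected to run until December 2026, so there is time to make the change before analysis. If the analysis plan already specifies visit-specific variances or robust standard errors, stating this is enough to answer the point about standard errors.
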